### Setting

The study will be conducted among professional and collegiate female volleyball teams in Hamedan Province, Iran. All screening, training sessions, and outcome assessments will be performed in the Sports Rehabilitation Laboratory at Bu-Ali Sina University, equipped with 2D motion analysis systems, a foot scan plate, EEG and EMG equipment, and supervised by experienced sports medicine and rehabilitation professionals.

### Participants

#### Recruitment.

Female volleyball players aged 18–23 will be recruited from club-level and collegiate teams in Hamedan Province, Iran, through direct communication with coaches and team announcements. Information sheets outlining the study objectives, inclusion criteria, potential benefits, and the lead investigator’s contact details will be distributed to these teams. Interested players will be invited to the Sports Rehabilitation Laboratory at Bu-Ali Sina University for eligibility screening.

Screening will involve two cognitively loaded motor tests, the Tuck Jump Test and the Single-Leg Landing Task, to assess DKV. Only participants meeting the inclusion criteria based on screening results will provide informed consent and proceed to randomization. The research team will conduct recruitment and screening, with completion expected within one month.

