### Screening procedures

All potential participants will complete two screening assessments in the Sports Rehabilitation Laboratory:

*1- Tuck Jump Test with Cognitive Task:* Participants will perform continuous tuck jumps for 10 seconds while responding to visual stimuli. The test will be video-recorded and assessed for neuromuscular deficits associated with DKV [21].

*2- Single-Leg Landing Task with Cognitive Task:* Participants will perform single-leg landings from a 30-cm box while completing a visual discrimination task. Landing mechanics will be captured using 2D motion analysis techniques to quantify knee valgus angles. DKV will be defined as a peak knee valgus angle greater than 12 degrees during the single-leg landing task, consistent with established thresholds for increased ACL injury risk [22].

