### Informed consent

All eligible participants will receive detailed verbal and written information about the study objectives, procedures, potential risks and benefits, and their right to withdraw at any time without penalty. Written informed consent will be obtained from all participants before enrollment. All procedures involving participants in this study will follow the guidelines of the Research Ethics Committee of Bu-Ali Sina University (IR.BASU.REC.1402.076) and adhere to the 2013 Declaration of Helsinki.

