### Outcomes

Participants will first receive detailed information about the study procedures, ethical considerations, and potential risks before providing informed consent and completing a personal information form. They will then undergo standardized instructions and a familiarization session, followed by a warm-up to standardize physical readiness and minimize injury risk. Assessments will be conducted 72 hours before the start of the eight-week neuromuscular-cognitive training protocol (pre-test) and within 72 hours after the final session (post-test) to evaluate its effects on modifiable ACL injury-related risk factors in female volleyball players with DKV. All assessments will take place in the Sports Rehabilitation Laboratory at Bu-Ali Sina University under standardized temporal and environmental conditions, with precise measures to control external variables and ensure accurate evaluation.

The primary outcome is the change in two-dimensional landing kinematics, particularly movement patterns associated with DKV, during single-leg landing under two conditions: with and without a concurrent cognitive task. Secondary outcomes include electrocortical brain activity measured by electroencephalography (EEG), lower limb muscle activity assessed by surface electromyography (sEMG), single-leg balance, lower limb muscle strength, and knee joint proprioception. These measures will determine the intervention’s impact on neuromuscular, cognitive, and biomechanical factors associated with ACL injury risk.

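### As written, athletes perform and are recorded in the screening jump and landing tests before giving informed consent, and those who fail screening never consent

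*Protocol article*

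**What the plan says.** All references are to the protocol article.

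- **Recruitment.** Information sheets go to the teams, and interested players are invited to the laboratory for eligibility screening. Then: "Only participants meeting the inclusion criteria based on screening results will provide informed consent and proceed to randomization". On who does this work: "The research team will conduct recruitment and screening, with completion expected within one month".
- **Screening procedures.** "All potential participants will complete two screening assessments in the Sports Rehabilitation Laboratory". The first is 10 seconds of continuous tuck jumps with responses to visual stimuli: "The test will be video-recorded and assessed for neuromuscular deficits associated with DKV". For the second, "Participants will perform single-leg landings from a 30-cm box while completing a visual discrimination task", and "Landing mechanics will be captured using 2D motion analysis techniques to quantify knee valgus angles". DKV is defined as a peak knee valgus angle above 12 degrees in this landing task.
- **Inclusion criteria.** DKV confirmed by the screening tests is one of the criteria.
- **Informed consent.** Detailed information, including potential risks, is given to eligible participants. On timing: "Written informed consent will be obtained from all participants before enrollment".
- **Outcomes.** "Participants will first receive detailed information about the study procedures, ethical considerations, and potential risks before providing informed consent". Familiarization, a warm-up and the assessments come after that.
- **Timeline, Fig 1 legend.** Enrolment and screening share the week before allocation and baseline assessment.
- **Implementation.** Eligibility is confirmed and consent obtained before randomization.

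**The concern.** The rule under Recruitment makes consent depend on a result that can only be obtained by carrying out study procedures. Those procedures are physically demanding and are recorded.

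The article itself treats such tasks as carrying some risk. The Background names single-leg landing as a typical ACL injury situation and says that cognitive load may worsen DKV. The Outcomes section adds a warm-up partly to reduce injury risk before the baseline tests.

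At stake is whether athletes know the risks and have agreed in writing before they jump, land and are recorded. A further question is what basis exists for holding the recordings and knee angles of athletes who fail screening and are never asked for consent.

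**Working it through.** No arithmetic decides this point, and the article gives no figure to reproduce. The check is whether the stated order of events allows consent before testing.

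1. **Can an athlete qualify to consent without being tested?** No. Recruitment limits consent to those who meet the inclusion criteria on the screening results. One criterion is DKV confirmed by the screening tests, which is defined by an angle measured in the landing task. Testing must come first.

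2. **Who is tested?** Under Screening procedures, all potential participants. This group includes those who turn out not to have DKV. Under the Recruitment rule they never reach the consent step.

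3. **Are these study procedures?** The research team performs them, in the university laboratory, to establish eligibility for this trial. The article does not call them research-only, but that is the fair inference.

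4. **Are they recorded?** The tuck jump test is explicitly video-recorded. The landing is captured by 2D motion analysis.

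5. **What information is described before the tests?** Recruitment describes information sheets covering objectives, inclusion criteria, potential benefits and contact details. Risks are not in that list. They appear under Informed consent, where the recipients are eligible participants, a status known only after step 1.

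6. **Do other sections give a different order?**

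| Section | Order described |
|---|---|
| Recruitment, with Screening procedures | invitation, tests, consent if the tests are passed, randomization |
| Informed consent | information to eligible participants, consent, enrollment |
| Implementation | eligibility, consent, randomization |
| Outcomes | information including risks, consent, familiarization, warm-up, assessments |
| Fig 1 legend | enrolment and screening in one week, then allocation and baseline |

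The second and third rows can be read in line with the first. The Outcomes row is in tension with it because it puts information and consent first. It does so before a landing from the same 30 cm height under cognitive load (Data collection methods) that athletes have already performed at screening. The Fig 1 legend leaves the order open: consent must precede enrollment, enrolment shares a week with screening, and nothing says which comes first within that week.

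7. **Is there a separate screening consent?** None is described in any section.

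8. **How many athletes?** If p is the share of screened athletes who qualify and go on to randomization, 30/p must be screened to randomize the target of 30. The article gives no value for p and no planned number screened. All that follows is that the 30 randomized athletes would themselves have been tested before consenting; the number who fail screening is unknown.

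**The case against.** The strongest reply is that the sections form one coherent sequence. Informed consent speaks of eligible participants and of consent before enrollment, Implementation puts eligibility before consent and randomization, and the Outcomes wording may mean first at the baseline visit. This stands in part. A reader might infer that Recruitment flatly contradicts the consent sections; the text does not support that. Only Outcomes is in tension, and the Fig 1 legend is unreconciled. But reading everything in line with Recruitment does not remove the problem. It confirms a plan to test and record before consent.

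A reader might also infer that screened athletes are left unprotected. That goes too far. Attendance is by invitation to interested players, information sheets are distributed, the laboratory is supervised by experienced professionals (Setting), ethics approval was granted (Study design), and Informed consent commits all procedures to the ethics committee's guidelines and the Declaration of Helsinki. Athletes who pass do consent later. None of this supplies written consent before the tests, or any consent from those who fail.

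Nor can it be asserted that athletes are told nothing of the risks. The article is a condensed account, and its summary of the sheet does not exclude a briefing at the visit. What can be said is that the described order places risk information after eligibility.

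A reader might add that the screening data of athletes who fail are needed for the CONSORT diagram. That does not follow: Maintenance strategy invokes the diagram for dropout and withdrawal, and counts of screened and excluded athletes do not require individual videos or angles.

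Finally, consent still precedes randomization, so the comparison of arms, the power and the primary analysis are untouched. That is correct, and it limits the point to participant protection.

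**Conclusion.** The point holds as one about the order of consent and screening. It rests on an explicit rule, not on detail that a condensed article has left out. The conclusion assumes that Recruitment is followed as written. If practice is to obtain consent first, the published text is wrong and needs correcting; if practice follows the text, the procedure needs correcting. The consequence has no statistical size, and the number of athletes concerned cannot be derived from the document. It should be corrected because it bears on participant protection and the remedy is cheap.

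**What to change.** - **Recruitment.** State that all interested players give written informed consent, including for video recording, before the screening tests, and that consenting athletes who meet the criteria proceed to baseline assessment and randomization.
- **Informed consent.** State that information on risks and the written consent come before any study procedure, including screening, and drop the restriction to eligible participants.
- **Screening procedures, Outcomes and the Fig 1 legend.** Reconcile these with that order, so that it is clear where consent falls relative to screening in the enrolment and screening week.
- **Implementation.** No change is needed; it fits either order.
- **Ethics committee.** Notify it of the change.

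The cost is a wording change, the notification, and a consent conversation with players who later fail screening. The design, sample size and analysis stay as they are.

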### Maintenance strategy

Several strategies will be used to minimize participant dropout. A study coordinator will send reminder text messages before each scheduled training and assessment session. Training sessions will be embedded within each team’s existing practice schedule to minimize scheduling conflicts with competitions and academic commitments. Where feasible, makeup sessions will be offered for absences due to illness or minor scheduling conflicts, provided the participant does not meet the withdrawal threshold defined in the Exclusion Criteria. Reasons for dropout or withdrawal will be systematically recorded and reported using a CONSORT flow diagram. Participants who complete the full protocol will receive individualized feedback on their landing mechanics as a non-monetary incentive to continue engaging.

### Screening procedures

All potential participants will complete two screening assessments in the Sports Rehabilitation Laboratory:

*1- Tuck Jump Test with Cognitive Task:* Participants will perform continuous tuck jumps for 10 seconds while responding to visual stimuli. The test will be video-recorded and assessed for neuromuscular deficits associated with DKV [21].

*2- Single-Leg Landing Task with Cognitive Task:* Participants will perform single-leg landings from a 30-cm box while completing a visual discrimination task. Landing mechanics will be captured using 2D motion analysis techniques to quantify knee valgus angles. DKV will be defined as a peak knee valgus angle greater than 12 degrees during the single-leg landing task, consistent with established thresholds for increased ACL injury risk [22].

### Inclusion criteria

Participants must meet all of the following criteria:

Female volleyball players aged 18–23 yearsMinimum of three years of competitive volleyball experienceCurrently training or competing at the club or collegiate level (minimum three training sessions per week)Presence of DKV confirmed by screening testsNo history of ACL injury or reconstruction in either kneeNo lower extremity injury in the past six months requiring medical attention or time away from sportAble and willing to participate in training sessions three times per week for eight consecutive weeksAble to attend all assessment sessions

### Exclusion criteria

Participants will be excluded if they meet any of the following:

History of ACL reconstruction or other knee ligament surgeryCurrent lower extremity injury or pain that limits participation in volleyball activitiesHistory of concussion within the past six monthsCurrent participation in other structured injury prevention or cognitive training programsUnable or unwilling to provide informed consentMissing two consecutive or three non-consecutive scheduled training sessions.

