### Intervention protocol

The intervention will be conducted over eight consecutive weeks, with three supervised training sessions per week, each lasting 60 minutes (a total of 24 supervised sessions). These will be scheduled within the teams’ regular training times to minimize disruption and enhance adherence. Sessions will be performed on non-consecutive days to allow adequate recovery. Each session will follow a standardized structure: Warm-up (15 minutes), including dynamic stretching, light aerobic activity, and sport-specific movements according to established protocols; main training (30–40 minutes), focusing on progressive neuromuscular and cognitive exercises; and cool-down (10 minutes), consisting of static stretching of the primary lower-extremity muscles and breathing exercises to facilitate recovery.

The intervention was structured as a four-phase progressive training protocol, consisting of consecutive two-week stages with specific objectives and gradual increases in motor complexity and cognitive demands (Tables 1 and 2).

**Table 1 pone.0353944.t001:** Categorization of exercises based on movement plane, limb involvement, and equipment use.

*Exercise Name*	*Sagittal (S)*	*Frontal (F)*	*Transverse (T)*	*Double Leg*	*Single Leg*	*Equipment*

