### Sample size

The sample size was calculated using G*Power software (version 3.1) for a repeated-measures ANOVA (within-between interaction) to detect changes in DKV angle at initial contact. The effect size was derived from the group × time interaction reported for DKV at initial contact in a previous neuromuscular training study with dual cognitive tasks [24] (partial η² = 0.19), converted to an effect size f = 0.48. Based on a significance level (α) of 0.05, statistical power (1-β) of 0.95, and an assumed correlation of r = 0.5 between repeated measures, a minimum total of 18 participants was required. The required sample size was initially determined based on the primary outcome measure (the DKV angle) to ensure sufficient statistical power. To adjust for multiple secondary outcome assessments and an estimated 20% attrition rate, we inflated the target enrollment to 30 participants, who will be randomly allocated in a 1:1 ratio to the intervention and control groups.

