### Concealment mechanism

To conceal allocation and prevent selection bias, the randomization sequence will be sealed in opaque, tamper-proof, sequentially numbered envelopes. Each envelope will contain a card indicating group assignment corresponding to the participant’s number. The envelopes will be opened only after completion of baseline assessments. An independent individual, not involved in study implementation, will prepare and manage the envelopes.

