### Statistical methods

Descriptive statistics, including means and standard deviations, will summarize the data. The Shapiro-Wilk test will assess data normality. Baseline characteristics will be summarized descriptively between groups. Repeated-measures ANOVA will be used to evaluate the group × time interaction effect as the primary indicator of intervention effectiveness (training vs. control; pre-test vs. post-test). Pairwise comparisons following significant interactions will be conducted with Bonferroni correction to control type I error. The five secondary outcome domains (cortical brain activity, lower-limb muscle activation, single-leg balance, muscle strength, and knee joint proprioception) will be interpreted as exploratory outcomes and hypothesis-generating findings. Partial eta squared will quantify effect sizes, interpreted as small (0.01), medium (0.06), or large (0.14). All analyses will be performed using SPSS version 27 with α = 0.05 and a 95% confidence level.

Given the modest sample size, supplementary analyses will be conducted. Baseline values will be reviewed descriptively, and if clinically meaningful baseline imbalance is observed, ANCOVA models adjusting for baseline values will be performed as sensitivity analyses. Missing data patterns will be assessed, and linear mixed models with appropriate covariance structures will be considered as sensitivity analyses to evaluate robustness under missing-at-random assumptions. Any meaningful discrepancy between supplementary analyses and the primary ANOVA will be reported and discussed.

To assess clinical significance and intervention effectiveness, minimal clinically important difference (MCID) and minimal detectable change (MDC) will be calculated at a 95% confidence level. The MDC will be derived using the standard error of measurement (SEM), as defined by the following formulas [28]:

$$\begin{array}{c} \text{SEM }=\;{\text{SD}}_{\text{pre}}\;\times \;\sqrt{(\text{1}-\text{ ICC})\;} \end{array}$$

$$\begin{array}{c} {\text{MDC}}_{\%\text{9}\text{5}}\;=\;\text{1}.\text{96 }\times \sqrt{\text{2}\;\times \text{ SEM}} \end{array}$$

$$\begin{array}{c} {\text{MCID}}_{\text{RCI}}=\;\text{1}.\text{96 }\times \;{\text{SD}}_{\text{pre}}\;[\sqrt{\left(\text{2}\times (\text{1}-\text{ICC})\right)}] \end{array}$$

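### An attendance rule that can only be met after randomisation is listed as an exclusion criterion and, on the most plausible reading, costs those athletes their post-test

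*Protocol article*

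**What the plan says.** The Exclusion criteria open with "Participants will be excluded if they meet any of the following". The last item in that list is missing "two consecutive or three non-consecutive scheduled training sessions".

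The Maintenance strategy refers to the same item. Where feasible, "makeup sessions will be offered for absences due to illness or minor scheduling conflicts", but only "provided the participant does not meet the withdrawal threshold defined in the Exclusion Criteria".

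Three other places fix how the rule works:
- **Timing.** Under Concealment mechanism: "The envelopes will be opened only after completion of baseline assessments". The Intervention protocol then schedules "a total of 24 supervised sessions".
- **Post-test.** Outcomes places it within 72 hours after the final session. The article makes no provision for assessing an athlete who has been withdrawn.
- **Analysis.** Statistical methods makes the group × time term of a pre/post repeated-measures ANOVA the primary indicator of effectiveness. As a fallback, "linear mixed models with appropriate covariance structures will be considered as sensitivity analyses", under a missing-at-random assumption.

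The Sample size section allows for "an estimated 20% attrition rate". It enrols 30 against a required 18.

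**The concern.** An eligibility criterion should be settled before allocation. This one depends on behaviour during training, so it selects among athletes who have already been randomised. If those who meet it are not post-tested, the primary comparison is between good attenders in each arm, and randomisation no longer guarantees that these groups are alike.

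Attendance may depend on the arm:
- The Blinding section puts the two arms on separate training days, so clashes with matches or classes can fall unequally.
- Makeup sessions are discretionary, and the trainers know the allocation.
- The experimental programme adds cognitive load.

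Attendance may also depend on the outcome, because pain, injury and low motivation all cause absence. The rule has no exception for injury, and injury is not among the stated reasons for a makeup session.

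The consequence is practical as well as analytic: no later analysis plan can recover a post-test that was never taken.

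**Working it through.** **1. When the rule can act.** Envelopes are opened after baseline and before training. A scheduled session can therefore be missed only by a randomised athlete. The term withdrawal threshold in the Maintenance strategy confirms that the rule applies to people already in the trial.

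**2. How strict it is.** With 24 sessions, an athlete stays in only if she attends at least 22 (22/24 = 91.7%) and has no two misses in a row. One missed week is three consecutive sessions and is enough.

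**3. The plan's own sample size.** Inputs from Sample size: partial η² = 0.19, f = 0.48, α = 0.05, power 0.95, r = 0.5, two groups, two time points.
- f = √(0.19/0.81) = 0.484, in line with the stated 0.48.
- G*Power's noncentrality for this interaction is λ = f²·N·m/(1 − r). At N = 18 this is 0.2304 × 18 × 2/0.5 = 16.59 on 1 and 16 degrees of freedom, giving power 0.968. At N = 16 power is 0.946. The smallest even total reaching 0.95 is 18, so the stated figure is reproduced. This point takes it as it stands.
- 18/(1 − 0.20) = 22.5, rounded up to 23. Enrolling 30 leaves 24 after 20% loss, and 18 remain up to a loss of 1 − 18/30 = 40%.

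**4. How often the rule would be met.** The documents give no absence rate, so p, the chance of missing any one session, is an assumption. Absences are taken as independent, with none made up. An athlete stays in with no misses, one miss, or two misses that are not adjacent. There are C(24,2) − 23 = 276 − 23 = 253 non-adjacent pairs, so

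P(excluded) = 1 − [(1 − p)^24 + 24p(1 − p)^23 + 253p²(1 − p)^22].

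At p = 0.05: 1 − [0.292 + 0.369 + 0.205] = 0.135, after rounding.

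| Assumed absence per session | Athletes meeting the rule | Expected of 30 | Expected left | Chance that fewer than 18 are left |
|---|---|---|---|---|
| 3% | 4.5% | 1.3 | 28.7 | 0.00 |
| 5% | 13.5% | 4.0 | 26.0 | 0.0001 |
| 8% | 32.4% | 9.7 | 20.3 | 0.14 |
| 10% | 45.8% | 13.8 | 16.2 | 0.67 |

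These rates fall if made-up sessions do not count as missed. If half of all absences were made up (again an assumption), 8% absence acts like 4%: 1 − [0.375 + 0.375 + 0.165] ≈ 0.08. Likewise, 10% acts like 5%, giving 13.5%.

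**5. What selection could do to the comparison.** This is an illustrative simulation with no true effect, 15 athletes per arm and completers only. Attendance is correlated 0.3 to 0.5 with the change score.
- Equal exclusion of 13% in both arms: no bias, type I error 5.0%.
- Exclusion of 27% versus 13%: bias 0.06 to 0.11 SD of change, type I error 5.2% to 5.8%.
- Exclusion of 44% versus 13%: bias 0.14 to 0.23 SD, type I error 5.8% to 8.0%.

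The exclusion rates and correlations are assumed. The pattern is the point: bias needs both a difference between arms and a link with response.

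**The case against.** A reader might infer that the protocol takes the post-test away from athletes who meet the rule. It does not say so. Exclusion could end training, assessment or analysis, and a condensed article commonly leaves follow-up of withdrawn participants and analysis sets to a fuller document. That stands, so loss of the post-test is an inference. It remains the most plausible reading of exclusion and withdrawal wording combined with a post-test tied to the final session.

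A reader might also infer that the trial will be underpowered. Enrolment of 30 against 18 absorbs 40% loss, which under the model above is reached only between 8% and 10% absence per session. Reminders, sessions built into team practice and makeup sessions should all reduce absence, although real absences may cluster. That objection largely stands, and power is not the main issue.

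Differential loss is not shown. Controls get the same exercises, frequency, duration and phases, and being held in a phase is not an absence. This stands as well: the bias is conditional.

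It would be too strong to say that the mixed model cannot handle these athletes. It can keep their baseline data under missing at random. However, it is only to be considered, as a sensitivity analysis. With two time points, an athlete without a post-test adds little information on change, and absence through pain, injury or motivation may not be missing at random.

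Finally, the attendance item does not name injury. Removal of injured athletes follows only from the lack of an exception. Harms are documented and withdrawals go into a CONSORT diagram, so the loss would be visible but not prevented.

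**Conclusion.** The point holds as a fault in stated conduct. A rule that can be met only after randomisation is placed among the exclusion criteria and treated as withdrawal. Followed as written, it most plausibly leaves a primary comparison of athletes selected on attendance.

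Its size cannot be fixed from the documents. Under independent absences with none made up, 4.5% to 46% of athletes would meet the rule as per-session absence runs from 3% to 10%, and fewer if made-up sessions do not count. Bias requires exclusion that differs by arm and relates to response; in the illustrations it ran from 0.06 to 0.23 SD of change. Without that combination, the cost is mainly precision, and the enrolment margin covers much of it.

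The documents do not support saying that post-tests are certainly lost, that the arms will certainly differ, or that the sample size fails.

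**What to change.** - Move the attendance item out of the Exclusion criteria. State there and in the Maintenance strategy that meeting the threshold does not end study participation, so that the two sections agree.
- Invite every randomised athlete to the post-test in the planned calendar window, whatever her attendance, and analyse her in her randomised arm.
- Use the threshold only to define a secondary per-protocol analysis, and report attendance by arm.

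Whether training or makeup sessions continue for an athlete who meets the threshold is a separate decision and is left to the investigators. For that reason the threshold should not simply be deleted from the Maintenance strategy, since it also governs who is offered makeup sessions.

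The cost is a change of wording and a few more post-test appointments. The estimated effect may be slightly smaller, because it will include athletes who trained less. The change has to be made before post-tests are missed.
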